### Ethical issues

The study was approved by Tianjin Nankai Hospital Institutional Review Board (IRB) on 17 December 2015 (IRB Approval No. 201504901P). After IRB approval had been obtained, this study was registered at an authoritative clinical trial registration platform (the Chinese Clinical Trial Registry) before the start of the study (ID: ChiCTR-IPR-15007643). Informed consent forms were developed in accordance with the requirements of the Declaration of Helsinki. All qualified subjects can freely choose whether or not to participate in this study and will be required to sign the informed consent form before taking part.

### Randomization

Complete randomization will be performed using the random number generator in SPSS 19.0; patients will be randomly assigned to the APP therapy group or the APP sham stimulation group. To reduce selection bias and confounding factors, the randomization will be performed by a single specifically appointed investigator. Each group will contain an equal number of participants. When a qualified subject participates in the trial, the recruiters will obtain the subject’s sequence number from the assigning investigator; the two groups will be assigned to separate wards to prevent communication between them. Thus, bias will be reduced further.

To prevent researcher bias from confounding the results, the randomization will be blinded using the sealed envelope method: the subject recruiters and evaluators will not be informed of the allocation sequence, and the allocation sequence will be placed in sequentially numbered, opaque, sealed envelopes (to ensure that the contents cannot be seen, even under bright light). To prevent the allocation sequence from being disrupted, the subjects’ names and dates of birth will be written on the envelopes, the envelopes will be sealed, and detailed information regarding the subjects will be recorded in a video. The information will be copied onto assignment cards, which are contained in the envelopes, using carbon paper, and a second researcher will watch the video to confirm that the envelopes are still sealed after the subjects’ names are written. A video recorder will be used to record the complete process of opening the envelopes.

### Blinding methods

We will ensure that the evaluators of treatment efficacy are unaware of the group assignments of the subjects by (1) blinding the subject data and (2) using independent statisticians. Moreover, the data will be analyzed by statisticians who are unaware of the group assignment. Thus, operators, evaluators, data administrators, and statisticians will work independently in this study.

### Intervention

After surgery, all the included subjects will lie in the supine position without a pillow and fast. The subjects will be given a liquid diet on the day after surgery. The APP therapy (or sham therapy) will be performed 6 h after the operation and every 12 h subsequently, for six treatment sessions, each lasting 3 min. The first evaluation will be performed 6 h after the operation, immediately before the first treatment. The patients will be then evaluated once every 12 h, for seven evaluations. The acupuncture points will be selected on the basis of the Nogier auricular point diagram [8]. Specifically, CO7 will be selected (the anterior 1/3 between the helix crus/part of the helix and the AB line, i.e., the auricular concha zone 7; Fig. 2). Operators will bring the required tools to the subject’s bedside and help the subject assume a comfortable position. The operator will then hold the upper posterior corner of the helix with one hand, and find the sensitive points with an auricular point detector (XS-100A; Guangzhou City Strong Medical Technology Co. Ltd., Guangzhou, China) using the other hand. The area will be disinfected using 75 % alcohol, and the vaccaria seeds will be attached to the auricular points.

**Fig. 2 Fig2:**
[figure not shown]
Auricular point acupressure

### Experimental group

Pressure will be applied to both ears alternately without rubbing (to avoid skin damage and infection at the acupuncture point). Optimal pressure will be considered to have been achieved when the subject feels localized tingling pain; the vaccaria seeds will then be fixed to prevent them from coming loose. We use small adhesive tape with spherical vaccaria seeds to adhere to the auricular points, and then, we press the points with digital pressure for 10 s. A 3-s pause occurs between each two pressings. After every intervention, we will remove the tapes. We will use the Visual Analog Scale (VAS; Fig. 3) to evaluate pressure intensity [9]. In accordance with preliminary experiments, the pressure intensity will be controlled at 50 mm. Because the pre-operative fasting time is relatively long, and stimulation of acupuncture points can lead to reduced blood sugar levels, it is necessary to observe whether the subject displays symptoms such as paleness and apathy during the treatment. If such symptoms appear, then the procedure will be ceased immediately, a blood sugar test will be performed, and treatment will be administered as necessary.

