### Control group

The subjects in the control group will receive sham APP, i.e., vaccaria-seed tapes adhered to the auricular points with no added pressure. Furthermore, to ensure ethical care and better communication with subjects in the control group, the subjects will be given health education (disease awareness, dietary guidance, exercise, and psychological care) during the treatment.

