### Outcome measures and participant timeline

#### Outcome measures

Baseline dataDemographic data will be recorded using a general information questionnaire, which we designed in house. The questionnaire includes questions on age, gender, education, occupation, weight, and height.Clinical characteristics will be recorded using another in-house-designed questionnaire. Specifically, data will be collected on the surgery time, anesthesia time, intraoperative blood loss, intraoperative fluid transfusion volume, and vital signs (temperature, heart rate, respiratory rate, and blood pressure).Primary outcome measureThe primary outcome is the time to first passage of flatus—we will begin observing and recording when subjects return safely to the ward, and the subjects and their families will be asked to record the time of the first passage of flatus. The interval between the two time points will be then calculated.Secondary outcome measuresTime to first defecation: We will observe and record when the subjects return safely to the ward, and the subjects and their families will be asked to record the time of first defecation. The interval between the two time points will then be calculated.Abdominal pain: The subjects’ degree of postoperative pain will be assessed using the VAS scale [10]. The first evaluation will be performed 6 h after surgery, immediately before the first treatment. Evaluations will then be carried out once every 12 h, for seven evaluations. Assistance will be given to subjects and their families in recording this information.Abdominal distention: The Likert scale will be used to assess the subjects’ degree of postoperative abdominal distention [11]. The first evaluation will be performed 6 h after the surgery, immediately before the first treatment. Evaluations will then be carried out once every 12 h, for seven evaluations. Assistance will be given to subjects and their families in recording this data.Nausea: The VAS scale will be used to assess subjects’ degree of postoperative nausea [10]. The first evaluation will be performed 6 h after the surgery, immediately before the first treatment. Evaluations will then be carried out once every 12 h, for seven evaluations. Assistance will be given to subjects and their families in recording this data.Vomiting: The frequency of postoperative vomiting will be recorded. The first evaluation will be performed 6 h after the surgery, immediately before the first treatment. Evaluations will then be carried out once every 12 h, for seven evaluations. Assistance will be given to subjects and their families in recording this data.Mental status: The Hospital Anxiety and Depression Scale (HADS) will be used to assess the subjects’ postoperative mental status [12]. The HADS consists of 14 items: seven assess depression, and the other seven assess anxiety. The scores of the anxiety and depression subscales are classified as follows: 0–7 points indicate no symptoms, 8–10 points indicate suspected symptoms, and 11–21 points indicate confirmed symptoms. The first evaluation will be performed 24 h before surgery, and the second evaluation will be performed on the day of discharge.Quality of life: the Gastrointestinal Quality of Life Index (GIQLI) will be used in this study [13]. The GIQLI aims to measure the quality of life of subjects with digestive diseases and includes five domains: subjective symptoms, physiological functional status, daily life, social activities, and psychological and emotional state. Within these domains, 36 items are assessed, each with a score from 0 to 4 points, for a total possible score of 144 points. The normal population will score 12–125 points. The first evaluation will be performed 24 h before surgery, and the second will be conducted 2 weeks after discharge. A follow-up evaluation will be carried out 1 month after discharge. Higher scores indicate better health status.Safety indicatorsAn event can be defined as an adverse event if at least four subjects suffer a symptom—such as local skin allergies, dizziness, and low blood sugar—during the treatment-evaluation period. These events will be statistically analyzed, and treatment safety is evaluated on this basis, in accordance with the research protocol. If serious adverse events occur, they will be immediately reported and managed accordingly.Participant timelineFor a complete overview of the time schedule of enrollment, interventions, and assessment for participants, see Fig. 4.

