### Data collection

To facilitate researchers in observing and recording various indicators, we have organized the content—outcome measures, observation time points, adverse events, and safety evaluations—into a case report form (CRF). Researchers are required to follow the requirements of the CRF as well as fill in the relevant information in a timely and accurate manner.

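### The in-session check for low blood sugar, and the test it triggers, are written for the APP arm only, so detection could differ between arms

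*Protocol article*

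**What the plan says.** The protocol article, section 'Experimental group', gives two reasons for watching the patient: the long fast before surgery, and the possibility that stimulating the points lowers blood sugar. It concludes that "it is necessary to observe whether the subject displays symptoms such as paleness and apathy during the treatment". If signs appear, "the procedure will be ceased immediately, a blood sugar test will be performed, and treatment will be administered as necessary".

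The section 'Intervention' covers what both arms share: posture, diet, schedule, locating the point, disinfection and attaching the seeds. Treatment runs "for six treatment sessions, each lasting 3 min". It contains no symptom check and no blood sugar test. The section 'Control group' begins "The subjects in the control group will receive sham APP", describes tapes without pressure, and adds health education. It contains no check or test either.

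Under 'Outcome measures', the safety indicators name symptoms "such as local skin allergies, dizziness, and low blood sugar". A symptom counts as an adverse event only if at least four subjects have it. The safety analysis then gives the number and incidence of each adverse event in both groups and compares them by the χ² test or Fisher's exact test.

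**The concern.** Low blood sugar is confirmed by a measurement. If the sign that prompts the measurement is acted on in one arm only, the two counts need not be comparable even when the true risk is the same. The fasting reason applies to sham subjects as well. The other reason, an effect of stimulation, is what a between-arm safety comparison would examine, so expecting it does not justify looking in one arm only.

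Three things are at stake:

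- The recorded count per arm could shift, probably against APP.
- Untested sham cases could keep the total below four. Low blood sugar would then not count as an adverse event in either arm, which would hide any APP cases too.
- A sham subject who turns pale or apathetic during a session has no written trigger for a test.

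**Working it through.** **1. Is there a common trigger anywhere?**

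| Section | Symptom check in session | Triggered blood sugar test |
|---|---|---|
| Intervention (both arms) | no | no |
| Experimental group | yes | yes |
| Control group | no | no |
| Data collection (CRF) | no; lists "outcome measures, observation time points, adverse events, and safety evaluations" | no |
| Quality control (operator training) | no | no |

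The CRF records events in all subjects, but recording an event does not prompt a test.

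**2. Reach of the check**

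- Sessions fall at 6, 18, 30, 42, 54 and 66 h. Total time is 6 × 3 = 18 min.
- Seven evaluations 12 h apart span 6 × 12 = 72 h = 4,320 min. 18/4,320 = 0.42%.
- The shared fasting reason applies mainly before oral intake: "The subjects will be given a liquid diet on the day after surgery". Assume that operations end between 08:00 and 18:00 and that the first liquid meal is at 07:00 the next day. The meal then comes 13 to 23 h after surgery, so one or two sessions precede it: 3/4,320 = 0.07% or 6/4,320 = 0.14%.

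**3. Worst case: no sham case tested**

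The text does not say whether the four subjects are counted over both arms. They are pooled here.

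- A true 3 v 3 is six subjects and counts. Recorded as 3 v 0, it does not count.
- A true 4 v 4 is recorded as 4 v 0. With 25 per arm that is 4/25 = 16% v 0%.

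Two-sided Fisher P values:

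| Recorded | 25 per arm | 21 per arm |
|---|---|---|
| 3 v 0 | 0.235 | 0.232 |
| 4 v 0 | 0.110 | 0.107 |
| 5 v 0 | 0.0502 | 0.048 |
| 6 v 0 | 0.022 | 0.021 |

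The 25 is the planned number per arm, and the 21 is the number per arm before the dropout allowance.

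**4. Chance that four or more cases are recorded**

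Let *p* be the in-session risk per subject, equal in both arms, and *d* the share of sham cases detected. All APP cases are taken as detected. The recorded total is Bin(25, *p*) + Bin(25, *p·d*). Both *p* and *d* are assumptions, because the document gives neither.

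| *p* | *d* = 1 | *d* = 0.5 | *d* = 0 |
|---|---|---|---|
| 2% | 1.8% | 0.7% | 0.1% |
| 5% | 24% | 12% | 3% |
| 10% | 75% | 52% | 24% |

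**5. Chance of a falsely significant difference (total ≥ 4 and Fisher P < 0.05)**

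| *p* | per arm | *d* = 1 | *d* = 0.5 | *d* = 0 |
|---|---|---|---|---|
| 10% | 25 | 0.9% | 1.3% | 3.3% |
| 10% | 21 | 1.3% | 1.9% | 5.2% |
| 20% | 25 | 2.2% | 8.6% | 38% |

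At 2% and 5% with 25 per arm the chance is about 0.1% or less. The 20% row shows that a low figure depends on a low risk. Nothing in the document supports a rate that high within 18 minutes of sessions.

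**The case against.** The strongest reply is that the point rests on where a sentence stands in a condensed article. The Control group section describes the sham by how it differs from APP and does not restate shared handling. The sentence "After every intervention, we will remove the tapes" also appears only under 'Experimental group', yet nobody would infer that sham tapes stay on. Operators were trained on an operational protocol that is not shown and may cover both arms. Nothing says that sham subjects go unobserved: experienced nurses attend both arms, and the CRF takes adverse events from everyone. Part of the rule, stopping pressure, has no sham counterpart. The loss of events below four subjects comes from the four-subject definition, which would drop events even with equal detection. The two effects also pull in opposite directions: extra APP cases count against APP, while falling below four hides them.

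Much of this stands. Placement is weak evidence of intent, no detection in the sham arm is a worst case, and no net direction of bias is established. The four-subject rule is a separate weakness, although unequal detection makes it bite harder. What the reply does not remove is that the article writes out a specific action for one arm, on grounds that partly cover both, for an event it will compare between arms. That is more than detail left to another document.

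**Conclusion.** The concern holds as a minor point, with low confidence. As written, a triggered blood sugar test exists for the APP arm only, so in-session detection of low blood sugar is open to being unequal. The size cannot be computed from the document. On the assumed risks of 2% to 10%, the main effect is on whether low blood sugar is counted at all (at 5%, from 24% down to 3% in the worst case). A false significant finding is unlikely. These figures assume equal true risk in both arms, full detection under APP and a threshold pooled over both arms. The primary outcome and the sample size are not affected.

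**What to change.** State the symptom check and its blood sugar test trigger in the common 'Intervention' section, applied identically at every session in both arms and recorded on the same CRF page. The reason specific to stimulation can stay under 'Experimental group'. Which signs trigger a test, and how a low value is treated, are for the investigators.

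The cost is a change of wording and an occasional extra blood sugar test. Sham subjects already have the same six bedside sessions with an operator. If equal checking was always intended, the change only makes that plain.

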**Fig. 3 Fig3:**
[figure not shown]
Visual analog scale

### Control group

The subjects in the control group will receive sham APP, i.e., vaccaria-seed tapes adhered to the auricular points with no added pressure. Furthermore, to ensure ethical care and better communication with subjects in the control group, the subjects will be given health education (disease awareness, dietary guidance, exercise, and psychological care) during the treatment.

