### Sample size estimation and statistical analysis

#### Sample size estimation

This study consists of two groups; the sample size-estimation formula is therefore based on a two-group, parallel, controlled design:$$ n=\frac{{\left({\mathrm{Z}}_{1-a/2}+{\mathrm{Z}}_{1-\beta}\right)}^2\times \left({\sigma}_1^2+{\sigma}_2^2\right)}{\delta^2}, $$where *n* represents the sample size in each group, σ represents the standard deviation, and *δ* represents the between-group difference with clinical significance. At an α value of 0.05, a power of 80 %, and given a two-sided test, we obtained Z scores of Z_1 − *a*/2_ = 1.96 and Z_1 − *β*_ = 0.84 from the Z score table. Eight subjects recruited from November 2015 to December 2015 were included in the pilot trial, and the primary outcome measure was the time to first flatus: *S*_1_ = 3.14 and *S*_2_ = 5.58. A decrease of 4 h in the time to first flatus was set as our clinical expectation based on preliminary tests and clinical experience. The above data were used to estimate the value of the overall parameter to be inserted into the above formula, and an n-value of 20.09 was obtained. Therefore, the rounded sample size in each group was 21; assuming a 15 % dropout rate, the final sample sizes in the experimental and control groups would be 25 cases, yielding the required 50 cases.

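### As written, only the control arm receives health education; unless the APP arm receives it too, the trial compares APP with sham plus education

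*Protocol article*

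**What the plan says.** The Control group section defines the sham as seed tapes without pressure. It then adds a second component: "to ensure ethical care and better communication with subjects in the control group, the subjects will be given health education". The content and timing are given as "health education (disease awareness, dietary guidance, exercise, and psychological care) during the treatment".

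The Intervention section sets the care for every included subject: supine position, fasting, and then "The subjects will be given a liquid diet on the day after surgery". It does not mention education. The Experimental group section covers tapes, pressing ("Pressure will be applied to both ears alternately without rubbing"), control of pressure intensity and watching for low blood sugar. It does not mention education either. Under Quality control there is operator training and uniform terminology, but no education for both arms.

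The Abstract, Design and Randomization sections all name the comparison as APP against APP sham stimulation. Randomization adds a further difference between the arms: "the two groups will be assigned to separate wards to prevent communication between them".

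**The concern.** A sham arm is there so that the arms differ only in pressing. Here the control arm receives a four-part co-intervention that the text does not give to the other arm. Education then coincides exactly with allocation. The t test, repeated-measures ANOVA and rank-sum test in the Statistical analysis section compare the arms as delivered, so none of them can separate education from pressing.

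The content of the education overlaps with outcomes measured after it is given. Psychological care bears on HADS, for which "the second evaluation will be performed on the day of discharge". Advice on disease, diet and mood bears on GIQLI, for which "the second will be conducted 2 weeks after discharge", with a further evaluation at 1 month. The Discussion wants quality of life to show the longer-term effects of the therapy. A null result, or one favouring control, on these scales could come from pressing that does nothing or from education that helps.

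**Working it through.** **1. Which arm gets what, as the text stands**

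| Component | APP arm | Control arm | Section |
|---|---|---|---|
| Supine, fasting, then liquid diet | yes | yes | Intervention |
| Seed tapes | yes | yes | Experimental group; Control group |
| Pressing | yes | no | Experimental group; Control group |
| Health education | not stated | yes | Control group |
| Ward | one ward | another ward | Randomization |

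Pressing is the intended difference. Education and ward are two others tied to allocation.

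**2. The plan's own sample size**

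Inputs from Sample size estimation: SDs 3.14 and 5.58, difference 4 h, Z values 1.96 and 0.84, dropout 15%.

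- Variance sum: 3.14² + 5.58² = 40.996.
- n = (1.96 + 0.84)² × 40.996 / 4² = 20.09, rounded up to 21 per arm.
- 21 / 0.85 = 24.7, so 25 per arm and 50 in total.

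The stated figures reproduce and are not in dispute.

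**3. Direction of the bias**

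Let p be the benefit of pressing and e the benefit of education. The expected contrast is p − e.

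- If p > e > 0, a real benefit of pressing is shrunk.
- If p = 0 and e > 0, the expected contrast is −e, in favour of control. All tests are two-sided, so this can reach significance.
- In neither case does a helpful e make a false claim of APP benefit more likely.

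Illustration for p = 0, using an ordinary t test with 21 per arm, 40 df, noncentrality e × √(21/2), and e in SD units (assumed). HADS and GIQLI will be analysed by rank-sum test and repeated-measures ANOVA, so this shows only the order of magnitude.

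| e (SD) | Noncentrality | Two-sided rejection (nominal 5%) |
|---|---|---|
| 0.2 | 0.65 | about 10% |
| 0.3 | 0.97 | about 16% |
| 0.5 | 1.62 | about 35% |

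Nearly all of these rejections favour control.

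**4. Flatus, as illustration only**

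Sessions fall at 6, 18, 30 h and so on after surgery. The preliminary means in the Background are 20.19 and 30.82 (taken as hours). Only the sessions at 6 and 18 h, and possibly 30 h, would therefore come before flatus. Diet is fixed for everyone. An effect of education on flatus is thus uncertain, and the document gives no figure for it.

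Assume that 4 h is the effect of pressing alone. SE = √(40.996/21) = 1.397 h. Noncentral-t power at 21 per arm is:

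| Assumed education effect | Net difference | Power |
|---|---|---|
| 0 h | 4 h | 80% |
| 0.5 h | 3.5 h | 69% |
| 1 h | 3 h | 55% |
| 2 h | 2 h | 29% |

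If the true gap is the preliminary 30.82 − 20.19 = 10.63 h, losing 2 h leaves 8.63 h and power stays above 99%.

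**5. What a change during recruitment recovers**

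With an assumed 1 h effect and a fraction f treated before the change, the expected difference is 4 − f.

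| f | Difference | Power |
|---|---|---|
| 0.25 | 3.75 h | 75% |
| 0.50 | 3.50 h | 69% |
| 0.75 | 3.25 h | 62% |
| 1 (no change) | 3.00 h | 55% |

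**The case against.** The asymmetry rests partly on silence. Nothing says that APP patients are denied education. The four topics could be ordinary ward nursing that a condensed article did not repeat, and the flow chart or the schedule of interventions could settle the matter. This stands as a reason to state the point conditionally. It does not remove the point: the article positively assigns the education under the control heading, for a reason specific to controls, and the section on care for all subjects leaves it out.

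The second objection is that no passage supports any size of education effect, and that the most striking figures concern flatus, the outcome least clearly affected. This also stands. A reader might infer from the 29% that the primary analysis is badly underpowered. The document does not support that. The sample size section says only "A decrease of 4 h in the time to first flatus was set as our clinical expectation", resting on preliminary tests and clinical experience. It does not say whether the preliminary controls had education, so the 4 h may already be the contrast as delivered, with no loss at all.

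The third objection is that any bias works against the sponsor's hypothesis in a single-center pilot, so it is harmless. A reader might go on to infer that no false positive can arise. That goes too far, because a significant difference favouring control is also an error when pressing has no effect. Only a false claim of APP benefit is ruled out as a consequence of helpful education.

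**Conclusion.** The point holds, on condition that the APP arm does not receive the education. On that condition the trial compares APP with sham plus education, and its analyses cannot attribute a difference, or the lack of one, to pressing. If education helps, the contrast shifts against APP: a benefit may be hidden or shrunk, or a spurious difference may favour control.

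HADS and GIQLI are the outcomes most plausibly affected. Flatus is uncertain. The size is unknown for all of them, and every rejection rate and power figure above rests on an assumed education effect. It would be too strong to say that the primary result is invalid or that the APP arm is known to go without education; the readable text shows neither. The point should be fixed, but it does not defeat the trial.

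**What to change.** State what the APP arm receives. If it already has the same education, one sentence under Intervention settles the point.

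If it does not, move the education from Control group to the care common to all subjects under Intervention, with the same content, timing and contact time in both arms. Trial status says that recruitment is ongoing, so record the date of the change and report patients treated before and after it. For those treated before, describe the comparison as APP versus sham plus education. If few patients remain, leave care as it is and use that description for the whole trial.

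The article does not say how often education is given. For at most 25 APP patients at an assumed 3 to 5 minutes each time, giving it once takes 75 to 125 minutes (about 1.3 to 2.1 nurse hours). Giving it at all six sessions takes 150 × 3 to 5 minutes = 7.5 to 12.5 hours. It also needs a protocol amendment and brief operator retraining.

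The main downside is a mixed comparison over two periods within 50 patients, too few to interpret each period alone. The separate wards remain a further difference between the arms, so this change does not by itself allow attribution to pressing alone.
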